**Online Questionnaire**				
	Demographics and health status		Self-report	
	Vegetarian/vegan status		Self-report	
	Dietary Habits		Dietary Habits Questionnaire	
	Attitudes and motivations towards food choice		Rationalizing meat consumption: The 4Ns Questionnaire [19]	
			The Food Choice Questionnaire [21] Ethical Food Choice Motives [18]	
			Dietarian Identity Questionnaire [20]	
**School visit**				
	Estimated usual dietary intake		Two 24-hour recalls, with adjustment of usual intake using MSM^a^	
	Height		Stadiometer	
	Weight		Body weight scales	
	Ulna Length		Steel measuring tape	
**Blood sample**				
	Hemoglobin		Cyanide-free photometry	
	Plasma ferritin		Immunoassay	
	Soluble transferrin receptor		Immunoassay	
	C-reactive protein		Immunoassay	
	Alpha-glycoprotein		Immunoassay	
	Zinc		ICP-MS^b^	
	Selenium		ICP-MS	
	Vitamin B12		Electrochemiluminescence immunoassay	
	Folate		Microbiological Assay	
**Urine Sample**				
	Iodine		ICP-MS	
**Accelerometry**				
	Average daily 24 h Activity		ActiGraph GT3x+, and accompanying wear time and sleep diary.	
		Average daily sleep		
		Average daily sedentary time		
		Average daily light intensity activity		
		Average daily moderate to vigorous intensity physical activity		

^a^MSM: Multiple source method

^b^ICP-MS: Inductively couple plasma mass spectrometry

#### Usual Dietary Intake

Dietary intake was assessed using two 24-hour diet recalls. The first recall was completed face-to-face by a Master of Dietetics student during the in-school data collection visit. The recall was performed using a multiple-pass technique. In the first pass, a “quick list” of all foods and beverages consumed during the previous day (midnight to midnight) is obtained. In the second pass, a detailed description is added to each food and beverage, including cooking methods, recipe information (where appropriate), and brand and product information. In the third pass, the amounts of each food and beverage consumed are obtained. Participants were asked to estimate the amount consumed for each food and beverage using standard household measures (cups, tablespoons, etc), food photographs, shape dimensions, food portion assessment aids (dried beans), and information from packaging. Finally, the full food list was reviewed and any additions or changes were recorded. Upon completion of the recall, participants were asked if salt was added to any of the food consumed, and if so, whether it was iodized. A second recall was completed over video call on a nonconsecutive day, with preference given, where possible, to performing the second recall on a weekend day. All 24-hour diet recalls were entered into FoodWorks dietary analysis software (version 9, Xyris Software) using the New Zealand Food Composition Database, FOODfiles (2016; The New Zealand Institute for Plant and Food Research Limited and the Ministry of Health) and nutrient data for commonly consumed recipes collated in the 2008/09 New Zealand Adult Nutrition Survey [22]. Dietary intake estimated for each nutrient of interest will be adjusted to represent usual intakes based on the estimated within-person variance of vegetarians and nonvegetarians using the Multiple Source Method [23]. Individual daily intakes from supplements will then be calculated and added to the usual intakes. The median (IQR) (for data that are not normally distributed) or mean (SD) (for data that are normally distributed) of daily intakes of energy and key macro- and micro-nutrients, and the main food sources of these nutrients will then be calculated. Molar ratios of phytate:zinc will be calculated to provide estimates of absorbable zinc. The estimated average requirement (EAR) cut-point method will be applied to the usual intake distribution to assess the prevalence of inadequate intakes with the exception of iron, for which the full probability approach will be used because of the skewed iron requirements as a result of menstruation in this population. [24].

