### Sample Size

A sample size of 300 adolescent girls from 13 secondary schools will have 80% power to the *P*=.05 level to detect a 0.5 standard deviation difference (a “moderate” difference) in continuous outcome variables between vegetarians and nonvegetarians, assuming a prevalence of vegetarianism of 20% and a design effect (for school clusters) of 1.5. If the prevalence of vegetarianism is much less than 20%, then purposeful sampling of vegetarians was planned in the second half of the recruitment year.

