### Statistical Analysis

Statistical analyses will be carried out using Stata (StataCorp). School clusters will be accounted for in all analyses using appropriate methodology (for example, with a sandwich estimator or as a random effect). Estimates of prevalence and means will be reported with 95% confidence intervals. A binary variable for vegetarianism will be created, and comparisons between vegetarians and nonvegetarians will be carried out using regression models: linear regression for continuous outcomes and logistic regression for binary outcomes.

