## Results

Recruitment and data collection were conducted and completed with 290 participants in 2019. Data are currently being cleaned and analyzed, with publication of the main results anticipated at the end of 2020.

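### Group comparisons of mean intake appear to use Multiple Source Method values as if observed, so their confidence intervals would be too narrow

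*Protocol article*

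**What the plan says.** Comparing dietary intakes between vegetarians and nonvegetarians is the first listed objective of the protocol article. Under Usual Dietary Intake, each girl gives two 24-hour recalls, and each nutrient is then "adjusted to represent usual intakes based on the estimated within-person variance of vegetarians and nonvegetarians using the Multiple Source Method". Supplement intakes are added after this step. Table 1 lists the adjusted usual intake as the dietary outcome.

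Statistical Analysis creates a binary vegetarian variable and compares the groups with "linear regression for continuous outcomes and logistic regression for binary outcomes". It promises 95% confidence intervals for means and prevalences. School clustering is the only source of dependence it corrects for, by a sandwich variance or a random effect. Nothing in the article carries the error of the adjustment into the comparison.

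**The concern.** A usual-intake adjustment removes day-to-day variation so that the spread of the values represents the spread between girls. That is what a distribution of usual intake needs, but it is not what the standard error of a group mean needs. Each girl still contributes only two days, so half of the within-girl variance remains in the sampling error of the mean. A regression on the adjusted values sees only the reduced spread. The clustering correction does not help, because it works on residuals that are already shrunk.

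The intervals for intake differences would therefore be too short, and differences between vegetarians and nonvegetarians would be declared more often than the nominal 5% when none exist. This touches every adjusted nutrient under the first objective, and the article intends its results to support dietary recommendations.

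**Working it through.** **The plan's own figure.** The Sample Size section gives "A sample size of 300 adolescent girls from 13 secondary schools" with "80% power to the *P*=.05 level" "to detect a 0.5 standard deviation difference", 20% vegetarians and "a design effect (for school clusters) of 1.5". The effective size is 300/1.5 = 200, that is 40 against 160. Then 0.5/√(1/40 + 1/160) = 2.83, and Φ(2.83 − 1.96) = 80.7%. The figure reproduces as two-sided. At the 290 girls reported under Results it is 79.4%. The sample-size statement is not in question.

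**Inputs for this point.** Two recalls per girl comes from Usual Dietary Intake. The ratio r of within- to between-girl variance is not in the article, so r = 0.5, 1, 2 and 3 are assumptions. It is also assumed that the adjusted values keep the between-girl variance, and that adjustment is within each group, as the wording suggests.

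**Formula.** Set the between-girl variance to 1 and the within-girl variance to r.
- A two-day mean has variance 1 + r/2 across girls, so the mean of n girls has variance (1 + r/2)/n.
- Adjustment within a group pulls each girl towards her own group mean. The group mean, and hence its true sampling error, is unchanged.
- The adjusted values have variance 1, so the regression reports 1/n.
- Reported/true SE = f = √(1/(1 + r/2)). Coverage of the nominal 95% interval = 2Φ(1.96 f) − 1.

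| r | f | SE too small by | Coverage | Type I error |
|---|---|---|---|---|
| 0.5 | 0.894 | 11% | 92.0% | 8.0% |
| 1 | 0.816 | 18% | 89.0% | 11.0% |
| 2 | 0.707 | 29% | 83.4% | 16.6% |
| 3 | 0.632 | 37% | 78.5% | 21.5% |

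**Simulation with clustering.** The set-up was 300 girls in 13 schools, 20% vegetarian, cluster sandwich SE, t on 12 df and 1,500 runs per scenario.
- Group-specific adjustment: for r = 1, 2, 3 coverage was 88–89%, 83–85% and 78%. With no true difference, the mean reported SE was 0.140, 0.138 and 0.139, against an actual SD of the estimate of 0.178, 0.203 and 0.229.
- Unadjusted two-day means, same model: coverage 93.8–95.4%, type I error 5.1%, 5.6% and 6.1%, and a true difference of 0.50 estimated as 0.49–0.50.

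**Supplements.** Suppose unshrunk supplement intake adds variance s, measured without error. Then f = √((1 + s)/(1 + r/2 + s)). With s = 1 and r = 2, f = √(2/3) = 0.82 instead of 0.71, and type I error is about 11% instead of 17%.

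**If the adjustment were pooled.** Girls would be pulled towards a common mean and the difference itself would be multiplied by f. A true 0.50 becomes 0.41, 0.35 and 0.32 for r = 1, 2, 3. The simulated test of no difference kept 4.9%, 4.8% and 6.1%, but coverage of the true difference fell to about 90%, 83% and 76%.

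**The case against.** The strongest reply is that the faulty step is inferred. No sentence says that adjusted values enter the regression. Usual Dietary Intake names descriptive summaries, food sources, phytate:zinc ratios and prevalence of inadequacy as their uses, and Statistical Analysis is a short general paragraph. The article is condensed, and an unseen analysis plan could add a bootstrap. This lowers confidence but does not remove the point. Table 1 defines the outcome, Statistical Analysis defines the model and its one variance correction, and followed as written they give the wrong standard error.

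The size is also open to challenge, and that part stands. The variance ratio is assumed. At 0.5 the loss of coverage is modest, and supplement intake dilutes it further. In the other direction, if the values were shrunk by f² instead of f, coverage by formula would be about 81%, 67% and 57% for r = 1, 2, 3.

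A reader might infer three stronger claims that the article does not support:
- That the estimated average requirement (EAR) cut-point prevalence is itself wrong. It is applied to the usual-intake distribution, for which the adjustment is suitable. Only the interval for a prevalence difference needs care.
- That logistic regression is prescribed for iron-inadequacy probabilities. The article assigns it to binary outcomes and nowhere feeds the iron probabilities into it.
- That differences are both falsely significant and attenuated. These belong to alternative readings. Attenuation arises only with pooled adjustment, which the wording makes less likely and under which the null test stays valid.

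**Conclusion.** The point holds for comparisons of mean dietary intake. On the plain reading, the standard errors omit the within-girl sampling error and the intervals are too narrow. The understatement runs from about 11% at a variance ratio of 0.5 to about 37% at a ratio of 3, and is smaller for nutrients where supplements contribute much of the variance. These figures rest on the assumed ratios, on group-specific adjustment, and on adjusted values that keep the between-girl variance.

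Biochemical, activity and questionnaire outcomes are unaffected. The error should be corrected before intake comparisons are reported. It does not rank as a defect that undermines the study, because it is confined to one family of outcomes and can be repaired with data already collected.

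**What to change.** State whether the adjustment is done by group, and how its error enters the comparisons. Then do one of the following for mean intakes:
- Fit a mixed model to the individual recall days, with vegetarian status as a fixed effect and girl and school as random effects. Transform skewed nutrients and handle supplement intake consistently.
- Bootstrap schools, repeating the adjustment, the supplement step and the regression in each resample.

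Keep the Multiple Source Method for usual-intake distributions and prevalence of inadequacy, and take intervals for prevalence differences from the same bootstrap, carried through the cut-point or probability step.

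No new data are needed, and the article reports that cleaning and analysis were still under way. The cost is some wording, some programming and wider intervals for the intake comparisons.

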### Objectives

Anecdotally, vegetarianism appears to be increasing in popularity. While this increase in popularity may confer some health benefits to the population, adolescent girls in New Zealand are already at an increased risk of inadequate intakes of iron and calcium, which would clearly be exaggerated if animal products were avoided. A poorly planned vegetarian diet can increase the risk of some nutrient deficiencies that may be exacerbated in female adolescents. Therefore, it is critical that the nutrient intake and status of vegetarian adolescent girls are assessed. Furthermore, assessing motivations, attitudes, and beliefs will further our understanding of dietary choices and inform the development of health promotion materials and programs targeted to this age group.

The aim of the SuNDiAL Project (Survey of Nutrition, Dietary Assessment and Lifestyles) is to compare the dietary intakes and habits, nutrition status, motivations, attitudes, and physical activity of a sample of vegetarian and nonvegetarian adolescent girls in New Zealand. The objectives of this study are to describe and compare the following between vegetarians and nonvegetarians:

Dietary intakes of macronutrients, free and added sugars, phytate, fiber, and key micronutrients (iron, zinc, vitamin B12, folate, iodine, and calcium)Biochemical status of key micronutrients (iron, zinc, vitamin B12, and folate)Attitudes toward and motivations for food choice (eg, the environment, animal welfare, health)Twenty-four–hour activity patterns (sleep, sedentary behavior, and physical activity)Dietary habitsWeight loss intentions

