## Discussion

Anecdotal reports suggest that the popularity of plant-based and vegetarian eating patterns may be rising in parallel with growing concerns about environmental sustainability. This pattern of eating is associated with some positive health outcomes [2,3,9]. Nonetheless, without careful planning, a vegetarian diet can increase the risk of inadequate intakes of bioavailable iron, zinc, calcium, and B vitamins [9,28]. The pubertal growth spurt combined with sexual maturation [12] increases the requirements for these nutrients, and therefore, we propose that female adolescents adopting a vegetarian diet may be at particular risk of nutrient inadequacy and deficiency.

The SuNDiAL project will provide a well-timed investigation into the dietary intakes, micronutrient status, physical activity, motivations, and beliefs of New Zealand adolescent girls. This project will also assess whether the current vegetarian diet consumed by adolescent girls in New Zealand offers substantial benefits or risks over a nonvegetarian eating pattern. The collection of biochemical data, dietary intakes, and 24-hour activity patterns will provide additional important details on benefits associated with vegetarianism, and the identification of individuals “at risk.” The results of this study will support the development of targeted interventions and recommendations aimed at enhancing the health, growth, and development of adolescent girls.

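### Micronutrient intakes are summarised only after supplements are added, with no food-only counterpart, and the plan does not settle whether the inadequacy and phytate:zinc steps include supplements

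*Protocol article*

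**What the plan says.** The Usual Dietary Intake section of the protocol article sets out a sequence.

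- Recall intake of each nutrient "will be adjusted to represent usual intakes based on the estimated within-person variance of vegetarians and nonvegetarians using the Multiple Source Method" (MSM below).
- Next: "Individual daily intakes from supplements will then be calculated and added to the usual intakes".
- Next come medians or means of daily intakes of energy and key nutrients, "and the main food sources of these nutrients will then be calculated".
- Two further steps follow without an ordering word. One is "Molar ratios of phytate:zinc will be calculated to provide estimates of absorbable zinc". The other is "The estimated average requirement (EAR) cut-point method will be applied to the usual intake distribution to assess the prevalence of inadequate intakes"; iron is handled separately, by a probability method.

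The first item under Objectives, to be compared between vegetarians and nonvegetarians, is "Dietary intakes of macronutrients, free and added sugars, phytate, fiber, and key micronutrients"; the micronutrients listed are iron, zinc, vitamin B12, folate, iodine and calcium. The Discussion adds: "This project will also assess whether the current vegetarian diet consumed by adolescent girls in New Zealand offers substantial benefits or risks". The Statistical Analysis section plans regression comparisons by a binary vegetarian variable and does not mention supplements.

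**The concern.** The questions are about an eating pattern, but the micronutrient intakes to be reported are food plus tablets. That total answers whether a group is adequately supplied by diet and supplements together. It does not show whether the diet alone would supply enough. If only the total is reported, a group whose food is short of B12, iron or zinc but who take supplements cannot be told apart from a group whose food is sufficient. Dietary recommendations, which the article says the results will support, would differ between the two cases.

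The phytate:zinc ratio raises a related point. It is meant to indicate how much zinc can be absorbed. If tablet zinc enters the denominator, the ratio no longer describes the balance of phytate and zinc in the foods eaten.

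**Working it through.** **The plan's own figures.** None bears on supplements. The only reproducible figure is the power statement: 300 girls, 20% vegetarian (60 against 240) and design effect 1.5 give effective sizes of 40 and 160. For 0.5 SD at two-sided 0.05 (sidedness is not stated) power is 0.807, which agrees with the stated 80%. This point leaves it unchanged.

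**Which steps include supplements?**

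| Step | Position in the text | Basis |
|---|---|---|
| Medians or means of daily intake | Stated to follow the supplement step | Food plus supplements |
| Phytate:zinc | Later sentence, no ordering word | Not stated |
| EAR cut-point (estimated average requirement) | Later sentence, applied to the usual intake distribution | Not stated |
| Probability approach for iron | Same sentence | Not stated |

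Read in sequence, the last three use the total. But the same paragraph uses the term usual intakes for the MSM-adjusted quantity before supplements are added, and Table 1 describes usual dietary intake as two recalls with MSM adjustment, without supplements. A food-only reading is therefore open. On that reading, reported intakes and reported inadequacy rest on different bases without the text saying so. Either way the basis needs stating.

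**Possible size for inadequacy.** All inputs are assumptions. Let p be food-only inadequacy and s the share using a supplement of the nutrient. If use is independent of food intake and lifts every user above the requirement, inadequacy on total intake is p × (1 − s).

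*Example A: p = 30% in vegetarians and 10% in nonvegetarians; nonvegetarian s = 10%.* The food-only gap is 20 points. Nonvegetarian inadequacy on total intake is 10% × 0.9 = 9%.

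- Vegetarian s = 20%: 24% − 9% = 15 points
- s = 30%: 21% − 9% = 12 points
- s = 50%: 15% − 9% = 6 points
- Equality needs 30% × (1 − s) = 9%, so s = 70%

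*Example B: p = 50% and 30%; nonvegetarian s = 10%.* The food-only gap is again 20 points. Nonvegetarian inadequacy on total intake is 30% × 0.9 = 27%.

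- Vegetarian s = 20%: 40% − 27% = 13 points
- s = 40%: 30% − 27% = 3 points
- s = 50%: 25% − 27% = −2 points
- Equality needs 50% × (1 − s) = 27%, so s = 46%

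*Equal use in both groups, Example B rates.* At 10% each the gap is 45% − 27% = 18 points. At 40% each it is 30% − 18% = 12 points. The absolute gap shrinks even without differential use, although the ratio of the two prevalences stays at 50/30 = 30/18 = 1.67.

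**Possible size for phytate:zinc.** The ratio is (mg phytate / 660) / (mg zinc / 65.4). With an assumed 1200 mg phytate and 9 mg food zinc it is 13.2; adding an assumed 10 mg of tablet zinc gives (1200/660)/(19/65.4) = 6.3. With 8 mg food zinc it is 14.9, falling to 9.1 with 5 mg and 6.6 with 10 mg of tablet zinc.

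**The case against.** Adding supplements after the MSM step is not a statistical error. Total intake is the relevant quantity for risk of inadequacy and for comparison with blood status, and the article also aims to assess nutrient intake and status and to identify girls at risk. A girl whose supplement meets her requirement is not at risk of inadequacy. All of this stands, and it is why total intake should be kept.

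A condensed article may also leave extra tables to the full protocol. That carries less weight here, because the article itself prescribes adding supplements before the summaries.

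A reader might infer that every intake, inadequacy and phytate:zinc figure includes supplements, so that no result describes the vegetarian diet. The documents do not support this. The order is fixed only for the intake summaries. Main food sources and dietary habits are planned outcomes that describe what is eaten, and supplements would be expected to change energy, macronutrients, sugars, fiber and phytate little. The point is confined to micronutrients.

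A reader might also infer that vegetarians supplement more, or that their diet will appear equal to the nonvegetarian one. The documents give no supplement rates or doses. In Example A the gap narrows but closes only at 70% use against 10%; in Example B it closes at 46% against 10%. These thresholds depend on the assumed rates and on every user being lifted above the requirement. If supplements were taken mainly by girls whose food intake was already sufficient, masking would be smaller.

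**Conclusion.** The point holds for micronutrients. The plan summarises their intakes with supplements included and names no food-only result, although its objectives and conclusions concern the diet. For the EAR, probability and phytate:zinc steps the defect is that the basis is not settled; it is not established that supplements are included.

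If supplement use is common, and more so if it is higher in vegetarians, the between-group difference in micronutrient adequacy from the diet itself is partly masked. On the assumed inputs a 20-point gap falls to between 15 and 6 points in Example A, and from 13 points to a 2-point reversal in Example B. The true size cannot be derived from the documents. This is a worthwhile, inexpensive improvement, and it does not invalidate the total-intake analysis.

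**What to change.** In the Usual Dietary Intake section:

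1. Report each micronutrient's intake and inadequacy by group twice: from food and beverages only, as the basis for statements about the vegetarian diet; and as total intake including supplements, as the basis for overall adequacy. State which is used at each EAR and probability step.
2. Compute the phytate:zinc ratio from food zinc only, and say so.
3. Report supplement use by group for each key micronutrient.

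The cost is one more set of tables. The food-only usual intakes already exist as the intermediate step before supplements are added, individual supplement intakes are to be calculated anyway, and the Results section says the data were still being cleaned and analysed.

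A comparison of blood status restricted to girls not taking a supplement should be at most exploratory. It selects on a choice that known deficiency may prompt, and it shrinks a vegetarian group planned at about 60 (20% of 300).
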